# One-on-one and group-based physical activity intervention compared to a waitlist control for post-secondary student mental health and social well-being: A 3-arm parallel randomized controlled trial protocol

**DOI:** 10.1371/journal.pone.0330851

**Published:** 2025-08-29

## Abstract

**Introduction:**

Physical activity (PA) service provision in the post-secondary context is recognized as important for promoting student mental health. Nonetheless, most evidence is of poor quality and lacks critical information regarding how the PA programs are designed, delivered, and made accessible to students. This study will examine PA program effectiveness for student mental health and social well-being, as well as implementation processes to offer insight for future research and program scale-up.

**Methods and analysis:**

Post-secondary students who are physically inactive and experiencing poor mental health will be recruited. A 3-arm parallel Randomized Controlled Trial, using a hybrid effectiveness-implementation design, will be conducted using a collaborative implementation approach. The effects of 6-week supervised one-on-one and group PA, compared to a waitlist control will be examined, with outcomes assessed at baseline (T1), 6-weeks (T2), and 1-month follow-up (T3). Primary outcomes will include immediate post-program changes (T1–T2) in mental health indices, including anxiety, depression, psychological distress, and well-being. Secondary outcomes will include changes from baseline to follow-up (T1–T3) and maintenance effects from post-intervention to follow-up (T2–T3) in mental health indices, as well as changes in social well-being indices (i.e., social connectedness, social support), and PA behavior. A process evaluation will be conducted to explore contextual influences (i.e., fidelity, adherence, reach, acceptability) on the conduct of implementation across PA program delivery styles. Effectiveness data will be analyzed using linear mixed effects modeling. Process evaluation outcomes will be analyzed using a mixed methods evaluation.

**Dissemination:**

A knowledge mobilization plan to enhance dissemination of the findings to the intended audiences (i.e., sport and recreation professionals, mental health professionals, students, researchers) has been developed.

**Trial registration:**

ClinicalTrials.gov NCT06350877

## Introduction

For reasons related to the educational context (e.g., academic and financial pressures) and life-span characteristics (e.g., identity exploration, instability), post-secondary students are a vulnerable population for experiencing mental health concerns [1]. Providing targeted services for supporting post-secondary student mental health is critical for promoting adaptive trajectories of functioning, adjustment, and well-being across the lifespan [2]. Mental health services offered on post-secondary campuses vary in range and support including promotion and outreach programs, short-term therapy, crisis appointments, and social or peer support programs [3,4]. Despite the services available to students, barriers to help-seeking are widely reported [5,6]. Indeed, less than half of students who experience poor mental health are receptive to traditional mental health services (e.g., medication counseling), with many students preferring alternative or complementary services such as those focused on lifestyle [7,8]. As a result, research focused on the implementation of sustainable approaches for offering alternative and complementary mental health services on post-secondary campuses has critical implications for supporting students who may not access traditional services.

PA is one alternative and complementary treatment approach that could be widely offered as an evidence-based approach for supporting student mental and physical health [9–11]. In support of PA as an alternative and complementary treatment, there has been substantial endorsement of major guidelines supporting the use of PA for the prevention and treatment of mental health conditions across clinical and non-clinical populations [12]. Considering the strong support for PA in the prevention and treatment of various mental health conditions, research focused on enhancing the provision of structured and tailored PA programs for post-secondary student mental health is increasing and promising [13–15]. Yet, there are notable knowledge gaps and study design limitations, which are suggested to contribute to the poor translation of accessible and sustainable PA programs tailored toward student mental health in the post-secondary community [13,16].

First, research to date has predominantly summarized single-group designs with a lack of a control group and randomization. This contributes to limitations in the confidence and quality of the implications drawn from the synthesized studies. Second, there is a paucity of research exploring the effects of different delivery styles (i.e., one-on-one (1:1) vs. group) on primary (i.e., mental health symptomology reduction) and secondary (i.e., social support, social connectedness) outcomes. Group-based PA, in comparison to 1:1 delivered PA, may provide a less costly and less resource intensive intervention option, and may have unique benefits associated with exercising with others and peer-to-peer support [17,18]. Drawing on self-determination theory [19] and the social identity approach to health [20], group-based PA may activate psychosocial mechanisms (e.g., relatedness, social cohesion) that are particularly relevant for promoting mental health and well-being. Third, the maintenance effects of PA programs on mental health or sustained PA behavior change are largely unknown. As such, conclusions of achieving lasting change to mental health and sustained PA involvement are not possible. Lastly, researchers have predominantly focused on effectiveness outcomes (i.e., testing effects on relevant outcomes) with limited to no research exploring implementation outcomes (i.e., the practical aspects of delivering a program). The limited research on implementation outcomes precludes understanding how to implement successful programs that are accessible for students with poor mental health in the post-secondary community [16,21]. To improve our understanding of implementation outcomes and the translation of research into practice, hybrid effectiveness-implementation studies which integrate both effectiveness and implementation stages of intervention development are recognized as important [22,23].

### Objectives and hypotheses

Using a type 1 hybrid effectiveness-implementation study design [22], this three-arm parallel randomized controlled trial (RCT) will evaluate the effects of 1:1 and group-based supervised PA, compared to a 10-week waitlist control, among post-secondary students across three timepoints: baseline (T1), post-intervention (T2; 6-weeks), and follow-up (T3; 1-month post-intervention). Primary outcomes will include the immediate changes (T1–T2) in mental health indices (i.e., anxiety, depression, psychological distress, and well-being). Secondary outcomes will include changes from baseline to follow-up (T1–T3) and maintenance effects from post-intervention to follow-up (T2–T3) in mental health indices, as well changes in social well-being indices (i.e., social connectedness, social support), and PA behavior. The aims of the study include: (1) examining group differences between 1:1 PA delivery, group-based PA delivery, and the 10-week waitlist control arm on the primary and secondary outcomes; and (2) grounded in process evaluation recommendations [24], to explore implementation outcomes (i.e.,., reach, adherence, acceptability, fidelity) that may be linked to variation in primary and secondary outcomes while offering insight for wider dissemination. Based on evidence supporting various PA modalities for improving mental health [25], both 1:1 and group-based PA are hypothesized to be more effective than the waitlist control on primary and secondary outcomes, with no expected differences between the PA conditions on primary outcomes. Drawing on the social identity approach to health [20], it is hypothesized that group-based delivery will result in greater improvements in secondary outcomes including social well-being outcomes and maintenance effects compared to 1:1 delivery. However, 1:1 delivery is expected to yield more favourable implementation outcomes, due to its potential for stronger individualized support [14,26]. The results will provide novel insight into the effectiveness of different PA program delivery styles on student mental health, social well-being, and PA behaviour, while also offering implementation considerations to support the sustainability and scale-up of PA interventions across post-secondary campuses.

## Methods

### Trial design

A 3-arm parallel RCT assessing the intervention arms (1:1 and group-based PA delivery) compared to a 10-week control arm (waitlist control) will be conducted. A parallel arm design will be implemented, whereby students will be randomized to a study arm, and each study arm will be allocated a different intervention. The protocol adheres to CONSORT guidelines [27] and SPIRIT [28] recommendations for reporting of clinical trial protocols (see S1 Checklist). Ethical approval for the study was obtained November 24, 2023 (protocol # 45228) and the study was retrospectively registered on ClinicalTrials.gov (Study identifier: NCT06350877; Registered: April 2, 2024). The clinical trial was retrospectively registered due to the initial phase of data collection being focused on piloting and refining the data collection methods.

### Study setting

The trial will leverage the infrastructure and support provided by Sport and Recreation Services, Health and Wellness Services, and the Mental Health and Physical Activity Research Centre at the University of Toronto’s St. George campus. A collaborative implementation approach involving the knowledge-user groups (i.e., researchers, professionals in on-campus sport and recreation and mental health, students) will be used to gather insights on embedding tailored and structured PA programs for student mental health within existing sport and recreation, and mental health services on post-secondary campuses.

### Patients and public involvement

The study is informed by previous research on student perspectives of PA programming for mental health [29] and a mixed methods evaluation of the proposed PA intervention protocol, within a 1:1 delivery setting [14]. Student feedback will be collected throughout the study and used to inform insights for wider program dissemination and scale-up. Using a train-the-trainer model [30], the research team will collaborate with Sport and Recreation Services to provide standardized training in behavior change coaching and PA program delivery for mental health to certified student PA coaches. These trained and certified coaches will be responsible for delivering the PA intervention. Referral pathways from on-campus mental health and accessibility services will be examined. Consistent with type 1 hybrid effectiveness-implementation studies [22], process-related information on coach training and the referral pathways to the program will be collected to inform future testing and broader dissemination of educational tools and implementation guidelines. Input from on-campus mental health and sport and recreation professionals, as well as students, has informed the evaluation targets for the trial. Input emphasized the importance of examining the effectiveness of different PA delivery styles on broader well-being outcomes, such as social well-being. Knowledge-users (i.e., sport and recreation professionals, mental health professionals, students, researchers) will also be consulted during knowledge mobilization and dissemination to enhance the useability and uptake of the findings.

### Eligibility criteria

Post-secondary students will be recruited based on the following eligibility criteria: (a) a post-secondary undergraduate or graduate student enrolled either part-time or full-time; (b) fluent in English (e.g., proficiency in reading and verbal expression – written and oral); (c) able to attend in-person PA sessions at the campus athletics and recreation centre; (d) moderately or insufficiently active (≤ 23 units of weekly leisure activity) based on interpretation scores from the Godin Leisure-Time Exercise Questionnaire [GLTEQ; 31]; and (e) experiencing self-reported ‘poor’, ‘fair’ or ‘good’ mental health in the past month. Exclusion criteria will include: (a) physically active (24 units or more of weekly leisure activity); (b) unsuccessful PA clearance using the PA readiness questionnaire [PAR-Q^+^; 32]; and (c) self-reported ‘very good’ or ‘excellent’ mental health.

### Schedule of enrolment, interventions, and assessments

After screening for eligibility, students will be contacted to schedule an in-person intake session with a program coordinator for the trial to provide informed consent, complete the baseline assessment (T1), and conduct randomization. In the intervention arms and control arm, study outcomes will be assessed at baseline (T1), 6-weeks post baseline (T2), and at 1-month follow-up (T3). Aligning with SPIRIT [28] and CONSORT [27] guidelines intervention flow will be tracked (see Fig 1) and the schedule of enrolment, interventions, and assessments has been provided (see Fig 2). A 1-month follow-up was selected for the current study given that, to date, only one known study has examined the maintenance effects of PA interventions on student mental health outcomes [16]. The aim is to assess whether the 1-month effects observed in prior research can be replicated in the current context [33]. If such findings are observed, this follow-up period will provide an important foundation for future studies to evaluate the sustainability and longer-term impact of these interventions. To support student retention at T3, a modest financial incentive will be offered in the form of a $25 CAD gift card (student’s choice of Amazon, Indigo, or Starbucks). Students’ reasons for discontinuing the trial will be collected, no further data will be collected following withdrawal from the trial.

**Fig 1 pone.0330851.g001:**
[figure not shown]
Participant flow.

**Fig 2 pone.0330851.g002:**
[figure not shown]
Schedule of enrolment, interventions, and assessments according to the Standard Protocol Items: Recommendations for Intervention Trials.

### Allocation and blinding

Simple randomization will be used to allocate eligible students to the intervention arms using Research Randomizer [www.randomizer.org; 34,35]. Each student will be individually randomized, with an equal chance of being assigned to any of the three groups (1:1 PA, group-based PA, or waitlist control). While simple randomization may lead to unequal group sizes, block randomization was deemed unsuitable due to the risk of generating groups not comparable on covariates [34]. Stratified randomization was not possible given the continuous nature of student enrollment [34]. To account for the potential group size imbalance, primary statistical analyses will use linear mixed effects modeling, which are robust to unequal sample sizes and unbalanced data [36].

To minimize selection bias, allocation concealment will be used by having an investigator who will generate and assign random group allocations only after students have completed enrollment and the baseline (T1) assessment. Random allocations will be generated in real-time and not stored in advance. Students will be partially blinded in that students will be unaware of the purpose of group allocation or study hypotheses but will know they were assigned to an intervention arm or the control arm. To prevent care provider bias, PA coaches from Sport and Recreation Services will also not be informed about the purpose of group allocation or the study hypotheses. Investigators will not be blinded due to their roles in program coordination and statistical analyses. Recruiting an external individual to manage randomization, program coordination, and analyses is not feasible given the scope of the study and availability of resources. Nonetheless, several steps will be taken to minimize bias. Allocation concealment will be maintained until after baseline assessment, and analyses will follow the pre-specified plan outlined in this protocol paper. Outcome measures include open-ended and standardized self-report items, completed by students through a secure online data capture platform [REDCap; 37] without direct investigator involvement. The study protocol is also pre-registered to support transparency and reduce the risk of selective reporting.

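### The investigator who assigns each arm also generates it on the spot on a public website, which hides the next arm but does not stop a draw from being discarded and repeated

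*Protocol article*

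**What the plan says.** All references are to the protocol article.

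- **Tool and method** (Allocation and blinding): "Simple randomization will be used to allocate eligible students to the intervention arms using Research Randomizer", individually, "with an equal chance of being assigned to any of the three groups". The section gives the tool's public web address.
- **Who draws** (same section): concealment is to be achieved by "having an investigator who will generate and assign random group allocations only after students have completed enrollment and the baseline (T1) assessment". One role thus covers both generating and assigning.
- **When, and what is kept** (same section): "Random allocations will be generated in real-time and not stored in advance".
- **Blinding and independence** (same section): "Investigators will not be blinded due to their roles in program coordination and statistical analyses". It adds: "Recruiting an external individual to manage randomization, program coordination, and analyses is not feasible given the scope of the study and availability of resources".
- **Setting** (Schedule of enrolment, interventions, and assessments): students attend an in-person "intake session with a program coordinator for the trial to provide informed consent, complete the baseline assessment (T1), and conduct randomization".
- **Operations** (Trial arms): 1:1 students are matched with a coach immediately. A group starts only when 3–8 students have been allocated to it. Sessions in both intervention arms are expected to begin within a week of randomization. Switching arms after allocation is not permitted within the research protocol.

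The steps listed to limit bias are concealment until after baseline, a pre-specified analysis, self-report through REDCap and registration. The section mentions no locked list, log of draws or second-person check.

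**The concern.** Allocation can be compromised in two ways. Someone may foresee the next arm and decide whom to enrol, or someone may see the arm just drawn and decide not to accept it. Drawing in real time after T1 closes the first route but leaves the second open. The person who generates the result also assigns it, and no earlier sequence exists against which the assignment could be compared.

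The Trial arms section shows where ordinary pressure could arise. A group that lacks members cannot start, and a 1:1 student needs a coach at once. Because arms may not be switched later, the draw is the only point within the trial at which the arm could be influenced. No bad faith is needed: an inconvenient result could be treated as a false start.

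If redraws depended on features of the student that predict change, selection bias would enter the PA-versus-waitlist contrasts, the 1:1-versus-group contrast, or both.

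**Working it through.** The article gives no figure on this point, so there is none to reproduce. The check has two parts.

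**1. What the stated procedure prevents**

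| Threat | Feature of the plan | Result |
|---|---|---|
| Predicting the next arm | Simple randomization, no blocks, no list, draw after T1 | Prevented |
| Discarding a draw and repeating it | Same role generates and assigns; no fixed sequence; no log or check described | Not prevented by anything stated |

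**2. Scale, for illustration only**

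Inputs from the Sample size section: 114 students, about 38 per arm, planned d = .50 at T2. The steering rates and the prognostic advantage below are assumptions with no source in the article.

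*Shift in an arm mean.* Suppose 4 of 38 students are steered into an arm and their expected change is 0.5 to 1.0 SD more favourable, in the same SD units as d:
- 4/38 × 0.5 = 0.053 SD, and 0.053/0.50 = 11% of the planned effect.
- 4/38 × 1.0 = 0.105 SD, and 0.105/0.50 = 21% of the planned effect.

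*Would arm sizes reveal it?* Under simple 1:1:1 randomization the SD of one arm's size is √(114 × 1/3 × 2/3) = 5.03. Simulation gives a 95% range of about 28 to 48, and the largest and smallest arms differ by 10 or more in about 52% of trials. If 10% of all waitlist draws were redrawn once, 114 × 1/3 × 0.10 × 2/3 = 2.5 students would leave that arm, well inside this variation.

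*Baseline imbalance.* Assume that a fraction r of waitlist draws among students above the median of a standard-normal severity score is redrawn once.
- Redraws = 114 × 1/3 × 1/2 × r.
- Expected waitlist size = 38 − 2/3 × redraws.
- With k = 2r/3 and 0.798 = √(2/π), the baseline difference between the PA arms and the waitlist is 0.798 × k × [1/(2 − k) + 1/(4 + k)].

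| r | Redraws | Expected waitlist size | Baseline difference (SD) | Chi-square test of arm sizes gives p < .05 (simulated) |
|---|---|---|---|---|
| 10% | 1.9 | 36.7 | 0.04 | 5% |
| 30% | 5.7 | 34.2 | 0.13 | 9% |
| 50% | 9.5 | 31.7 | 0.22 | 18% |
| 100% | 19.0 | 25.3 | 0.51 | 63% |

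The simulated baseline differences agree: 0.041, 0.127, 0.218 and 0.515. Occasional redrawing would be small and would leave little trace in arm sizes. Only wholesale redrawing would probably show. These are differences in baseline level, not estimates of bias in the T1–T2 change.

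**The case against.** The strongest reply is that the finding leans on silence. The article says that allocations are not stored beforehand; it does not say that they go unrecorded. A journal article condenses a fuller protocol, which could describe a log, and the student may be present when the draw is made. This stands. A reader might infer that a repeated draw would go unseen and could never be detected, but the text supports only that no record or check is described.

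Three further inferences are tempting and go too far.

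- *One person meets the student, draws, coordinates and analyses.* Allocation and blinding refers to an investigator; the Schedule section refers to a program coordinator. Investigators collectively hold the coordination and analysis roles. No sentence joins all of these in one individual.
- *Concealment is absent.* It is not. The next arm cannot be predicted, and in that usual sense the article's use of the term is correct.
- *The analysis cannot deal with it.* This is too absolute. T1 is in the mixed model and the effect is a group-by-time interaction, so differences in baseline level are separated out. Steering related to later change would remain. Redraws made purely to fill a group or suit a coach need not be related to prognosis at all.

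The other listed safeguards do not close the gap. Self-report and a pre-specified analysis do not govern who enters which arm, and neither does registration, which the Trial design section describes as retrospective.

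Timing also limits the remedy. Recruitment and data collection are estimated to finish on 24 October 2025. Ten weeks earlier is 15 August 2025, before the article's publication on 29 August 2025. On that schedule few or no students remain to be randomized.

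**Conclusion.** The point holds as a weakness of the stated method, not as an error in any figure. Generation and assignment sit in one role within an unblinded team that also coordinates and analyses. The draw is made afresh on a public website with no fixed sequence, so a repeat is possible and nothing described would prevent it.

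There is no evidence that any draw was repeated. The size of any bias is unknown. The illustrative 0.05–0.11 SD depends wholly on the assumed 4 of 38 students and the assumed 0.5–1.0 SD advantage. Under the assumed redraw rule, a 10% rate gives a baseline difference of only 0.04 SD.

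The point is worth acting on because a better method is inexpensive and does not need the external person whom the article rules out. It should not be read as a claim that the randomization failed.

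**What to change.** **Any remaining enrolment.** Replace the website draw with a computer-generated list uploaded once by a team member who has no intake contact, and hide it from intake staff. Release one locked, time-stamped assignment per record, only after T1 is complete. The REDCap platform already in use could do this if its randomization module is available, which the article does not say. Otherwise, keep a time-stamped log of every draw, held by someone outside program coordination.

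**Students already randomized.** In the trial report:
- state what record of each draw exists;
- compare enrolment order, T1 completion time and allocation time, and report the result;
- say plainly that this comparison cannot reveal draws discarded on a separate website;
- describe this phase as protected against foreknowledge only.

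**Cost.** Some set-up work and an ethics board notification for the prospective part, and a short reconciliation for the retrospective part. No extra participants, visits or external staff are needed. If enrolment has closed, only the reporting steps apply.
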